## Abstract

**Background:**

The Pregnancy and Newborn Diagnostic Assessment (PANDA) system is a digital clinical decision support tool that can facilitate diagnosis and decision-making by health care personnel in antenatal care (ANC). Studies conducted in Madagascar and Burkina Faso showed that PANDA is a feasible system acceptable to various stakeholders.

**Objective:**

This study primarily aims to evaluate the effects of the PANDA system on ANC quality at rural health facilities in Burkina Faso. The secondary objectives of this study are to test the effects of the PANDA system on women’s satisfaction, women’s knowledge on birth preparedness and complication readiness, maternal and child health service use, men’s involvement in maternal health service utilization, and women’s contraception use at 6 weeks postpartum. Further, we will identify the factors that hinder or promote such an app and contribute to cost-effectiveness analysis.

**Methods:**

This is a randomized controlled trial implementing the PANDA system in 2 groups of health facilities (intervention and comparison groups) randomized using a matched-pair method. We included pregnant women who were <20 weeks pregnant during their first antenatal consultation in health facilities, and we followed up with them until their sixth week postpartum. Thirteen health centers were included, and 423 and 272 women were enrolled in the intervention and comparison groups, respectively. The primary outcome is a binary variable derived from the quality score, coded 1 (yes) for women with at least 75% of the total score and 0 if not. Data were collected electronically using tablets by directly interviewing the women and by extracting data from ANC registers, delivery registers, ANC cards, and health care records. The study procedures were standardized across all sites. We will compare unadjusted and adjusted primary outcome results (ANC quality scores) between the 2 study arms. We added a qualitative evaluation of the implementation of the PANDA system to identify barriers and catalysts. We also included an economic evaluation to determine whether the PANDA strategy is more cost-effective than the usual ANC strategy.

**Results:**

The enrollment ran from July 2020 to January 2021 due to the COVID-19 pandemic. Data collection ended in September 2022. Data analyses started in January 2023, ended in June 2023, and the results are expected to be published in February 2024.

**Conclusions:**

The PANDA system is one of the most comprehensive apps for ANC because it has many features. However, the use of computerized systems for ANC is limited. Therefore, our trial will be beneficial for evaluating the intrinsic capacity of the PANDA system to improve the quality of care. By including qualitative research and economic evaluation, our findings will be significant because electronic consultation registries are expected to be used for maternal health care in the future in Burkina Faso.

**Trial Registration:**

Pan-African Clinical Trials Registry (PACTR) PACTR202009861550402; https://pactr.samrc.ac.za/TrialDisplay.aspx?TrialID=12374

**International Registered Report Identifier (IRRID):**

DERR1-10.2196/37136

## Introduction

### Background

Antenatal care (ANC) is one of the strategies that contributes to reducing maternal and neonatal mortality. In the early 2000s, the concept of ANC was introduced and refocused to be more efficacious [1-3]. Essential activities such as the prevention of anemia and malaria in pregnant women, preparation for delivery and obstetric emergencies, and advice on good nutrition for women and newborns have found their place in the new vision of ANC [4]. In addition, the World Health Organization (WHO) guidelines recommend 8 antenatal visits to the clinic so that each point of contact will ensure a smooth and safe pregnancy [5]. According to the WHO, increasing the frequency of ANC visits for women and adolescents is associated with a reduced risk of stillbirths. These visits provide additional opportunities to detect and manage potential problems [5]. Additionally, regular antenatal visits to the clinic increase the chance of delivering at a health facility [6].

Despite the importance of ANC, data on the use of services by pregnant women remain scarce in sub-Saharan Africa [7-9]. Several reasons could explain this situation, including the quality of care and satisfaction of pregnant women with health services. Nikiema et al [10] showed that the different steps of ANC are not carefully adhered to, ignored, or misunderstood by health care providers in Burkina Faso. Tiembré et al [11] who evaluated the quality of ANC in Grand-Bassam (Ivory Coast) reported that the interpersonal communication skills of the health care providers with patients were poor. It is essential to systematically follow the different stages of ANC to provide quality care to pregnant women. One solution to improving the quality of ANC is the standardization of care, obliging health workers to systematically follow all the steps of ANC consultation [12-14]. Therefore, the use of mobile apps and telemedicine seems appropriate. The WHO insists on using mobile apps to provide maternal and child health care because these apps play an essential role in improving the quality of health care services [15]. In 2013, the World Health Assembly passed numerous resolutions on information and communication technologies in the health care sector. The use of apps in health care has been noted to be related to reduced health care costs, improved quality, and equitable access to health services [15]. The application of information and communication technologies in the health sector includes client education and behavior change, medical record management, electronic decision support, quality care in health services, human resource management, and supply chain management [16].

Concerning decision support and quality of care, ANC has been a particular focus of mobile app interventions. However, different studies [12-17] show contrasting results. In 2018, Chen et al [18] conducted a systematic review of 245 studies, including 51 randomized controlled trials, on the effectiveness and appropriateness of mobile apps for maternal and child health care between 2011 and 2016. Their results showed that mobile apps had no effect on the quality of health care in approximately half (43%) of the randomized controlled trials.

The Pregnancy and Newborn Diagnostic Assessment (PANDA) system [19,20] is a digital clinical decision support tool that facilitates diagnosis and decision-making by health care personnel in ANC. Feasibility and acceptability studies of the PANDA system have been conducted in Madagascar and Burkina Faso [14,21]. The study [21] conducted in the Koupéla district of Burkina Faso in 2016 with the nongovernmental organization, Enfants du Monde, Switzerland, showed that the PANDA system is a feasible tool for improving the quality of care for pregnant women and for collecting detailed information in the electronic form. The women in that study [21] expressed high satisfaction with the antenatal visits using this telemedicine system except for the average duration of ANC (women found that the average duration of ANC is high with the PANDA app), which would increase with the app use. The health care workers expressed their satisfaction with the service improvements and noted the different steps of ANC according to the recommendations of Burkina Faso. In the PANDA app, the different steps of ANC are presented in an imposed chronology to the health care provider. The completeness of the data for all fields conditions the passage from one stage to the next. Therefore, it is impossible to omit information. Following these encouraging results, the Ministry of Health of Burkina Faso expressed interest in using the PANDA telemedicine system for maternal and neonatal health care to improve the quality of care. Hence, we plan to implement a randomized controlled trial to evaluate the effectiveness of PANDA in improving the quality of ANC.

### Study Objectives and Hypothesis

The objective of this study was to evaluate the effects of the PANDA system on the quality of ANC in Burkina Faso. We hypothesize that the PANDA telemedicine system improves (1) the quality of ANC provided to pregnant women, (2) women’s satisfaction, (3) women’s knowledge on birth preparedness and complication readiness, (4) maternal and child health service use, (5) men’s involvement in maternal health service utilization, and therefore (6) postpartum contraception use.

### Study Setting

This study was conducted in Burkina Faso, where the ANC rate varies according to the area of residence. The 2010 Demographic and Health Survey and Multiple Indicator Cluster Survey (Burkina Faso Enquête Démographique et de Santé et à Indicateurs Multiples [EDSBF-MICS IV]) showed that 1.5% and 5.7% of the pregnant women did not attend antenatal visits in the urban and rural areas, respectively [22]. Moreover, according to the EDSBF-MICS IV, only 33.7% of the pregnant women have received at least 4 ANC consultations as recommended by the WHO. Only 41.2% of the women had their first ANC visit in the first trimester of pregnancy, and the median number of months of pregnancy at the first ANC visit was 4.4 months at the national level [22]. Among the women who received ANC for the most recent birth 5 years before 2010, only slightly more than half (53%) had been informed about the signs of pregnancy complications. In ANC, it is crucial for pregnant women to know the pregnancy danger signs. The EDSBF-MICS IV also showed that almost all women (95%) received ANC from a trained provider, and the majority (61%) of these trained providers were auxiliary birth attendants. Midwives provided ANC for 17% of the women, and nurses examined almost the same proportion of women (16%). Approximately one-third of the women (34%) had at least 4 antenatal visits, which aligns with the Burkina Faso Ministry of Health’s recommendations. There were significant differences between the areas of residence in Burkina Faso: in Ouagadougou (Burkina Faso’s capital), 54% of the women attended the 4 recommended visits compared with 38% in other cities and only 31% in rural areas [22]. The consequences of this low access to maternal, newborn, and child health services are high maternal and infant mortality rates. One in 8 children die before 5 years, and the maternal mortality ratio was 341 deaths per 100,000 live births in 2010 [22]. We chose the health district of Koupéla (Centre-East Region of Burkina Faso) because of its proximity to Ouagadougou. At that time, there were no ongoing ANC interventions in this district. The other reason for choosing this district is that the PANDA feasibility test was conducted in this district in 2016.

## Methods

### Conceptual Framework of This Study

Our research project consists of implementing an intervention called the PANDA telemedicine system. This study phase, which we call the interventional phase (as it follows the design and feasibility phases of the intervention), involves 2 groups of health facilities in the same district (an intervention group and a comparison group). We compared the effects of the intervention with those of the usual ANC offered in the comparison group through a cluster randomized trial. The interventional phase also employs qualitative research and a cost-effectiveness study at the end of the trial. The qualitative research identifies the barriers and catalysts of using the PANDA system for ANC in the intervention group. The cost-effectiveness analysis provides information on the costs of implementing the PANDA system in Burkina Faso. The expected effects of the app are improvement in (1) the quality of ANC provided to pregnant women, (2) women’s satisfaction, (3) women’s knowledge of birth preparedness and complication readiness, (4) use of maternal and child health services, (5) men’s involvement in maternal health service utilization, and (6) contraception use at 6 weeks postpartum. The long-term impact of this app is the reduction of maternal and neonatal mortality.

### Cluster Randomized Controlled Trial

#### Study Design

In this study, the intervention is the PANDA telemedicine system. It involves 2 groups of health facilities in the same district (an intervention group and a comparison group). The intervention group offered ANC using the PANDA app installed on tablets. Each health facility in this group had at least one tablet. The health centers in the comparison group offered ANC as usual (the PANDA app was not used in these health facilities). The rationale for implementing a cluster randomized trial is that the intervention (training and use of the PANDA system) cannot be implemented at the individual (pregnant woman) level but only at the health center level. The study design is shown in Figure 1.

**Figure 1 figure1:**
[figure not shown]
Study design. ANC: antenatal care; PANDA: Pregnancy and Newborn Diagnostic Assessment.

#### Participant Eligibility Criteria

The participants were pregnant women with gestational age between 14 and 20 weeks of amenorrhea, regardless of age, residence, and socioeconomic level. They were screened for eligibility for this study: first by health care workers on arrival and second by the data collectors of this study. Any pregnant woman who met the following criteria was eligible for this study: (1) <20 weeks of gestation, (2) belonging to the health facility area, (3) no plan to travel in the next 9 months (from inclusion in this study to 6 weeks postpartum), (4) not taking part in any other ongoing research, (5) volunteering to participate, (6) being in a clinical and obstetrical condition that allows delivery at the health center (no need to refer to the next level), and (7) has the intention to deliver in that health center.

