#### Outcomes

The primary outcome is a binary variable derived from the quality score. It will be coded 1 (yes) for women with at least 75% of the total score and 0 if not (Table 1). The quality score considers all the components of good ANC according to the gestational age of the pregnancy. The different components are grouped into 7 main dimensions with items. These items are derived from Burkina’s guidelines on ANC [23]. The categorization is that each woman has a total score for each ANC (from the first consultation to the last).

**Table 1 table1:** Summary of the components of quality antenatal care.

Item (1 if yes, 0 if no)	Data source
Antenatal consultation performed	Woman’s health card reports
Partner’s presence at the consultation	Item asked to the woman
Possession of a verified health record	Woman’s health card reports
Pregnancy test performed	Woman’s health card reports
Date of last period requested	Item asked to the woman
Probable date of delivery given to the pregnant woman	Item asked to the woman
Hypertension was investigated	Item asked to the woman
Asthma was investigated	Item asked to the woman
Testing for sickle cell disease	Item asked to the woman
Diabetes was investigated	Item asked to the woman
Surgical history was obtained	Item asked to the woman
Number of pregnancies was queried	Woman’s health card reports
Number of deliveries was queried	Woman’s health card reports
Number of abortions or miscarriages was queried	Woman’s health card reports
Number of caesarean deliveries was queried	Woman’s health card reports
Number of living children was queried	Woman’s health card reports
Alcohol consumption queried	Woman’s health card reports
Tobacco use queried	Woman’s health card reports
Sugar and albumin levels in the urine measured	Woman’s health card reports
Syphilis test performed	Woman’s health card reports
An HIV test was offered to the woman	Woman’s health card reports
HIV test was performed	Woman’s health card reports
Blood pressure measurement	Woman’s health card reports
Fetal heart sounds recorded	Woman’s health card reports
Search for edema of the feet and face	Woman’s health card reports
Weight gain	Woman’s health card reports
Temperature checks	Item asked to the woman
Physical examination: uterine height measured	Woman’s health card reports
Physical examination: vaginal touch performed	Woman’s health card reports

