Physical examination: decision on obstetrical prognosis (normal pelvis, borderline pelvis, etc)	Woman’s health card reports
Tetanus vaccination verified and performed	Woman’s health card reports
Hepatitis B vaccination verified and performed	Woman’s health card reports
Antianemia prophylaxis (iron–folic acid) prescribed	Woman’s health card reports
Antianemia prophylaxis: woman explains dosage correctly	Item asked to the woman
Prescribed antimalarial prophylaxis	Woman’s health card reports
Malarial prophylaxis: woman explains dosage correctly	Item asked to the woman
Danger signs of pregnancy explained to the woman	Item asked to the woman
Place of delivery discussed	Item asked to the woman
Importance of exclusive breastfeeding explained	Item asked to the woman
Early breastfeeding of the baby has been advised	Item asked to the woman
Maternal nutrition: good feeding practices discussed	Item asked to the woman
Postpartum contraception was discussed	Item asked to the woman
Use of an impregnated net was explained	Item asked to the woman
Newborn care was explained	Item asked to the woman
The childbirth preparation plan was discussed	Item asked to the woman
The woman was asked to raise concerns where appropriate	Item asked to the woman
The next meeting was negotiated	Item asked to the woman
Summary of the antenatal care written in the woman’s health record	Woman’s health card reports

The secondary outcomes to measure include the satisfaction of pregnant women (measured at each ANC), women’s knowledge on birth preparedness and complication readiness (measured in the first trimester and just before delivery), use of maternal health services, men’s involvement in health service use (defined as the proportion of men who accompany their wives to the health centers for ANC sessions and delivery and the proportion of men who attended an ANC session or delivery), and finally, the women’s use of postpartum family planning (measured at the sixth week postpartum).

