### Statistical Methods

Quantitative data were extracted and transferred to Stata 15.1 for analysis. We will perform an intention-to-treat and per-protocol analysis of the cluster randomized trial. The unit of analysis will be women. The analysis will compare the intervention and comparison groups’ unadjusted and adjusted primary outcomes results. Unbalanced factors between the 2 study groups will be used to adjust the intervention effects on the study outcomes. These factors will be women’s sociodemographic factors and women’s autonomy. The means and proportion comparison tests for independent samples will be used at the 5% threshold. In case of nonnormality of a quantitative variable (satisfaction scores, knowledge scores, etc), robust or Poisson regression will be used.

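### The eligibility section states two incompatible gestational-age windows, and gestational age at entry is left out of the named adjustment set

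*Protocol article*

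**What the plan says.** Entry rule:

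- Participant Eligibility Criteria, opening sentence: "pregnant women with gestational age between 14 and 20 weeks of amenorrhea".
- Same paragraph, numbered list: "Any pregnant woman who met the following criteria was eligible for this study: (1) <20 weeks of gestation". There is no lower limit.
- Abstract, Methods: "<20 weeks pregnant during their first antenatal consultation in health facilities".
- Results: the inclusion limit is again under 20 weeks, with no floor.

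Timing of the first knowledge measurement:

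- Outcomes: "measured in the first trimester and just before delivery".
- Data Collection Methods: at inclusion and at the end of pregnancy.

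Score and adjustment:

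- Outcomes says the quality score takes the components of care "according to the gestational age of the pregnancy", and that each woman has a score at each visit.
- Data Collection Methods makes the number of antenatal visits attended one of the service-use measures.
- Statistical Methods: "Unbalanced factors between the 2 study groups will be used to adjust the intervention effects on the study outcomes". The next sentence names those factors as sociodemographic characteristics and autonomy. Other Variables illustrates the former with age, education, marital status, residence and occupation. Gestational age is in neither group.

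**The concern.** Two windows in one paragraph cannot both have been the screening rule. Which one applied decides whether women in the first three months of pregnancy belong to the trial population, and so to whom the result applies.

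The second issue follows from the first. Gestational age at entry governs which elements of care fall due and how much pregnancy remains in which to attend visits. If it differed between arms, the stated adjustment rule would not pick it up, because the rule confines adjustment to two groups of factors that do not contain it. This is more than a detail left to an analysis plan: the article says what the set will be. The setting is one in which such a difference could arise, since centers were randomized before women were enrolled, staff knew their center's arm, and providers made the first eligibility screen.

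**Working it through.** **1. The plan's own figure.** The only stated size is 264 women per group.

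- Inputs (Sample Size section): 65% vs 80%, power 80%, 5% error (taken as two-sided), 40 women per center, ICC 0.015, 10% loss.
- Two-proportion formula: 138 per arm without continuity correction, 151 with it.
- Design effect: 1 + (40 − 1) × 0.015 = 1.585.
- 138 × 1.585 = 218.7 and 151 × 1.585 = 239.3. Both round up to 6 centers of 40, which is 240.
- 240 × 1.10 = 264, which reproduces the stated figure.

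Gestational age does not enter this calculation, so the point leaves the sample size unchanged.

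**2. The entry rules side by side.**

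| Woman's gestational age | 14 to 20 weeks | Under 20 weeks |
|---|---|---|
| Below 14 weeks | not eligible | eligible |
| 14 to below 20 weeks | eligible | eligible |
| Exactly 20 weeks | eligible if the limit is inclusive | not eligible |

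The first row is a firm contradiction. The last depends on how the limit is read. The Abstract's first-consultation condition does not clash with either set of limits; it is an extra condition that the numbered criteria do not contain.

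**3. Is the disputed group small?** Study Setting reports that 41.2% of women nationally made their first visit in the first trimester (2010 survey). That is a share of all women, so among those arriving before 20 weeks the share would be larger if the figure held locally. The article gives no local figure.

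**4. Other text that bears on the floor.**

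- On the usual convention that the first trimester ends before week 14 (the article does not define it), a 14-week floor leaves essentially no one for a first-trimester knowledge measurement. The under-20-week rule also admits women past the first trimester. The at-inclusion timing fits either window.
- The travel criterion spans 9 months from inclusion to 6 weeks postpartum. Assuming a 40-week term, entry at 14 weeks leaves 40 + 6 − 14 = 32 weeks, about 7.4 months. Nine months is about 39 weeks, which corresponds to entry near 46 − 39 = 7 weeks. This shows strain with the floor but does not settle the question.

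**5. Room for visits (assumed 40-week term).**

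- Entry at 20 weeks leaves 40 − 20 = 20 weeks.
- Entry at 14 weeks leaves 40 − 14 = 26 weeks, a ratio of 26/20 = 1.3.
- With no floor, entry at 8 weeks (an illustrative value, not in the article) leaves 32 weeks, a ratio of 32/20 = 1.6.

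These compare individual women, not arms.

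**6. Possible shift in the primary difference.** Shift = (difference in the chance of reaching 75% between earlier and later entrants) × (difference between arms in the share of earlier entrants). Both inputs are assumed, each ranging from 5 to 30 percentage points:

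- 0.05 × 0.05 = 0.25 points
- 0.10 × 0.10 = 1 point
- 0.20 × 0.20 = 4 points
- 0.30 × 0.30 = 9 points

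The planned effect is 15 points.

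**The case against.** - **The under-20-week limit is well supported.** The numbered criterion, the Abstract and the Results agree on it, and one descriptive sentence stands apart. This stands. A reader might infer that the trial population cannot be identified at all; that goes too far. What remains is a contradiction to be corrected by whoever knows which rule was applied.
- **Screening had a second step.** A reader might infer that unblinded providers applied different readings by arm. The eligibility section says data collectors screened as well. Data Collection Methods gives each collector one intervention and one comparison center, and has a coordinator check recruitment. The collectors were not blinded either, and a later sentence in that section describes their assignment less clearly. Even so, a shared second screener makes arm-specific readings less likely, and none is documented.
- **The 423 vs 272 enrollment is not evidence of differential recruitment**, tempting as that reading is. The qualitative section takes the intervention group as its target, speaks of 7 health centers and counts the only semiurban center among them. The arms are therefore 7 and 6 centers, with the unmatched center on the intervention side. If the six pairs recruited equally (an assumption), that center would account for the whole excess of 423 − 272 = 151. Counts by center are not given.
- **The score may already be scaled to what is due at each gestational age.** This is a fair reading of Outcomes. It would reduce the dependence of the primary outcome on entry timing, without clearly removing it, and it does nothing for the visit count.
- **Adding a covariate with no demonstrated imbalance is a matter of preference.** This has some force. But the variable is tied to the score and to the visit count by construction, and it was needed for eligibility.

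**Conclusion.** The point holds in two parts.

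First, the entry window is stated in two incompatible ways in one paragraph, with an unmatched first-consultation condition in the Abstract and conflicting timings for the first knowledge measurement. These passages must be reconciled; the article does not establish which window was used.

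Second, the named adjustment set excludes gestational age at entry. Its consequence is a risk, not a demonstrated bias: gestational age by arm is not reported, so the effect cannot be sized from the article. The 0.25 to 9 point range rests wholly on assumed inputs, and its upper end needs large differences on both counts. The concern is most direct for the number of visits and weaker for the primary outcome. The sample size is unaffected.

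**What to change.** 1. State one entry window, the one actually applied at screening, in the Abstract, Participant Eligibility Criteria and Results. Say whether week 20 is included and whether entry had to be at the first consultation.
2. Give the first knowledge measurement a single timing in Outcomes and Data Collection Methods, matching when it was in fact taken.
3. Keep every enrolled woman in the intention-to-treat set. Report gestational age at inclusion by arm, and the number outside the window by arm.
4. Include gestational age at inclusion in the adjusted model whether or not it is unbalanced. The Results section reports analysis complete in June 2023, so if this model was not already planned it should be labelled post hoc.
5. Add a sensitivity analysis restricted to women who satisfy every stated version: at least 14 and under 20 weeks, at their first consultation.

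The cost is wording, a few lines of a baseline table and one model term; eligibility screening required gestational age, so no new data should be needed. There are two downsides. The extra term is added with only 13 clusters. Gestational age may also have been recorded with different completeness or accuracy by arm, because the app forces every field to be completed and asking the date of the last period is itself a scored item. Missing gestational age should therefore be reported by arm as well.
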